#### 2.8.3. Secondary outcome: feelings of school-based support

The secondary outcome will assess students' perception of quality of relationships with teachers/administrators, school connectedness, and social and emotional satisfaction at school. These school-based outcomes will be assessed with the emotional support form from the NIH toolbox emotion measures at all three time points (35, 36).

#### 2.8.4. Additional levels of data collection

Additional sources of data will be collected to explore how access to iDECIDE may impact changes in student- and school-level outcomes as well to define potential barriers to and supports of scalable implementation.

##### 2.8.4.1. Annual school-wide survey

In the fall semester of each academic year, schools will be asked to distribute a brief, de-identified survey during a school period, following an opt-out parental consent process. The purpose of the survey is to examine over time how implementation of iDECIDE impacts prevalence of substance use and perceptions of school as a supportive environment. Other domains queried in the survey include race and ethnicity, sexual identity and gender identity (37), perceived discrimination (38), and physical and emotional health (39–42).

##### 2.8.4.2. Pre-post curriculum survey

All students who participate in the iDECIDE curriculum will have the opportunity to complete a brief, anonymous survey immediately prior to the first curriculum session and immediately following the last curriculum session. Students will be provided a link to the pre- and post-survey by the trained iDECIDE facilitator. Domains queried include past seven days of substance use, perceived harm of substance use, knowledge of drug effects, and satisfaction with the curriculum.

##### 2.8.4.3. Key stakeholder interviews

At the point of randomization, schools will be given the opportunity to nominate three to five key school and community stakeholders. Nominated stakeholders will be (1) school faculty involved in responding to substance use related infractions and/or planning or delivery of social-emotional supports at participating school, or (2) community members (e.g., local coalition leaders, identified by the participating school to be trained in and deliver the iDECIDE intervention to school students). Stakeholders will complete a one-hour recorded semi-structured interview with a member of study staff ~two school months prior to being trained in iDECIDE and approximately six school months after implementation. Interviews will include prompts and questions to address beliefs, attitudes, and perceived effectiveness of substance use policies in their school, as well as structural factors that may contribute to transition to non-punitive responses to substance use in a school-based setting. A waiver of written consent was requested for this portion of the research protocol in which stakeholder participants will be provided a fact sheet detailing the interviews and verbal consent will be gathered at the beginning of each interview.

### 2.9. Confidentiality

Per standard school substance use policy, parents are notified by the school in the event of a substance use infraction. For this reason, parents will be aware of their student's substance use, and seeking consent to participate in the study will not inadvertently reveal student substance use habits to parents/guardians. Beyond basic eligibility criteria revealed in consent documents, no information will be shared with parents/guardians of participants under the age of 18 except when required by law (e.g., acute concern for safety of self or others; suspected child abuse). Confidentiality will be maintained by numerically coding all data and by keeping all data in password-protected, secure, HIPAA-compliant databases. All study staff will be trained in the protection of privacy of research participants and will have certification from the Collaborative Institutional Training Initiative. This study will maintain a Certificate of Confidentiality from the National Institutes of Health to protect against forced disclosure of identifiable, sensitive information collected as part of this clinical trial.

### 2.10. Data analysis

#### 2.10.1. Overarching statistical model

The two primary outcomes will be assessed at three time points: (1) immediately after a student is first caught for a substance use infraction (i.e., baseline, *time-of-infraction*); (2) 45 days after the date of the first infraction (i.e., *45 day-follow-up*); (3) 90 days after the date of the first infraction (i.e., *90 day-follow-up*). The proposed primary outcomes (items correct on a knowledge survey and number of days out of 14 spent using a preferred substance) are both bounded counts variables. We therefore will assume (a) whether an item is correct on the knowledge survey follows a Bernoulli distribution and the number of days out of 14 spent using a substance follows a binomial distribution, and (b) these distributions (both the binomial and Bernoulli) are governed by a latent probability parameter. This latent probability describes either the likelihood of getting an item correct on the knowledge survey or the average number of days spent using a preferred substance out of 14, and the log-odds for a student's latent probability at the three assessment time points is described following a trivariate normal distribution. This statistical model will allow us to examine changes in substance use and knowledge about substances while controlling for (1) measurement error, and (2) correlations between repeated measures collected over the three time points. The means for the log-odds of the latent probabilities can be further decomposed into a summation of population-level, school-level, and student-level effects. The specific decomposition of the means for the log-odds will depend on the outcome measure.

The complexity of the statistical models (e.g., a multivariate latent measure model with both fixed and random effects and with observed data distributed as counts) is most easily handled within a Bayesian framework. However, prior distributions will need to be defined for model parameters. A conservative approach will be taken using only weakly informative priors with a diffuse range (for example, standard deviations for log-odds will be set to 2.5, estimates for fixed effects will be centered at 0, and we will use empirical Bayes priors for intercepts).

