**Figure 1 F1:**
[figure not shown]
Stepped wedge schema.

Data collection will occur during both unexposed and exposed study phases. School staff will refer students with school-based substance use infractions to the study team as close to the time of infraction as possible through an online, secure referral system. Referrals will be submitted while schools are in both unexposed and exposed study phases. Once referred to the study team, students will be given the opportunity to enroll in a three visit study. Baseline visits will occur as close as possible to the receipt of school referrals to establish information most representative of thoughts, feelings, and behaviors at the time of the initial infraction. Follow-up visits will occur ~45 and 90 days after the baseline visit to ascertain thoughts, feelings, and behaviors occurring after the time of the school response to the substance use infraction, which may or may not involve iDECIDE depending on whether the school is in the unexposed or exposed phase of the study. Study procedures will take place remotely, at the student's school, in a private space at a local public library, or at the Massachusetts General Hospital (MGH) lab based on the preferences of the school, student, and/or parent/guardian.

This trial has been approved by the Mass General Brigham (MGB) Institutional Review Board (IRB). The trial will be conducted in accordance with the Consolidated Standards for Reporting Trials (CONSORT) statement (25–28) and will be reported here in accordance with the Standard Protocol Items: Recommendations for Intervention Trials (SPIRIT) statement (29, 30).

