### 2.7. Interventions

#### 2.7.1. Discipline as usual

Standard disciplinary responses given by each partnering school will be used as the control during the unexposed phase of this trial. Standard responses may include detention, Saturday school, in-school suspension, out-of-school suspension, expulsion, citation, or any other punitive or non-punitive response given by schools per their existing policy at the point of a violation of school substance use policy. Students will report on the school response to the infraction during the baseline assessment.

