### 2.8. Outcome measures

Assessments will occur at baseline (proximal to the point of the initial infraction), and ~45- and 90-days following baseline. Primary, secondary, and exploratory outcomes are described below. All measures, including descriptives and potential covariates, are listed in Table 2.

**Table 2 T2:** Time and events.

**Assessments**	**Baseline (V1)**	**45-day follow-up (V2)**	**90-day follow-up (V3)**

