#### 2.8.2. Primary outcome: frequency of substance use

Substance use behavior will be assessed by how many days of the past 14 days a student spent using their preferred substance. Self-reported substance use will be assessed at all visits using the Timeline Followback (33, 34). A 90-day recall period will be queried at enrollment, and a modified Timeline Followback will be administered at subsequent visits to ascertain substance use in the period between visits.

Urine samples will be collected at all three visits to biochemically verify self-reported use. A 10-panel qualitative rapid dip drug test (Medimpex United Inc.) will be performed, qualitatively assessing for amphetamines (limit of quantitation [LOQ] = 1,000 ng/mL), cocaine (LOQ = 300 ng/mL), barbiturates (LOQ = 300 ng/mL), methamphetamines (LOQ = 1,000 ng/mL), benzodiazepines (LOQ 300 ng/mL), opiates (LOQ = 2,000 ng/mL), cannabinoids (THC) (LOQ 50 ng/mL), phencyclidine (LOQ = 25 ng/mL), oxycodone (LOQ = 100 ng/mL), and methadone (LOQ = 300 ng/mL). Quantitative urinary assays will also be completed at all visits (Dominion Diagnostics, North Kingstown, Rhode Island, USA). The quantitative assay includes creatinine-normalized 11-nor-9-carboxy-THC levels (CN–THCCOOH; LOQ: 5 ng/mg; upper limit of linearity: 500 ng/mg) using liquid chromatography–tandem mass spectrometry, and cotinine via enzyme immunoassay (EIA; LOQ: 500 ng/mL; upper limit of linearity: 2,000 ng/mL). Study staff will mail collection kits in advance of virtual visits to participants, and participants will provide the sample during the videoconferencing session. Qualitative results will be shown to the assessor during the visit, and kits will be shipped overnight for quantitative assays.

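### The analysis counts time from the infraction but the visits count from a later baseline, so the untreated 14-day use window can include post-infraction days and bias the phase contrast if the lag or early response differs by phase

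*Protocol article*

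**What the plan says.** The protocol article gives two time origins.

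- **Analysis (2.10.1).** Baseline is "immediately after a student is first caught for a substance use infraction" and is labelled time-of-infraction. The follow-ups are "45 days after the date of the first infraction" and "90 days after the date of the first infraction".
- **Design (2.1) and outcomes (2.8).** "Follow-up visits will occur ~45 and 90 days after the baseline visit"; 2.8 repeats this as approximately "45- and 90-days following baseline".

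The baseline visit follows several steps. The school refers (2.1), the study team contacts the family, and consent and assent are obtained before any further study procedure (2.4). For virtual visits, urine kits are mailed ahead (2.8.2). The article aims to keep these steps close to the infraction but gives no maximum interval.

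The use outcome is "how many days of the past 14 days a student spent using their preferred substance", assessed at all visits (2.8.2). The same section adds: "A 90-day recall period will be queried at enrollment". Section 2.7.1 says: "Students will report on the school response to the infraction during the baseline assessment". Section 2.10.4 codes the effect variable 0 at the time of infraction and makes its interaction with exposed phase the primary analysis. It tests use for non-inferiority and states a threshold odds ratio of 1.045.

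**The concern.** The two origins agree only if the baseline visit falls on the day of the infraction, and the consent process makes that unlikely. A 14-day window counted back from a later visit mixes days before the student was caught with days after. Some of those later days may follow the school's response, since the student is asked to report that response at the same visit. The model nevertheless treats the whole window as the pre-treatment value.

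What is at stake is the contrast between phases. If the interval from infraction to visit, or the immediate change in use after being caught, differs between unexposed and exposed phases, the two baselines are shifted by different amounts and the interaction absorbs the difference. A difference is plausible. The immediate response is what the trial varies, and school staff make the referrals while knowing whether their school has been trained; 2.6 blinds only outcome assessors and, at first, the analyst. The non-inferiority threshold is narrow, so a small differential shift can matter.

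**Working it through.** No figure in the plan tests this point directly. The power of 0.82 for seven waves rests on school-level enrolment and infraction data that the article does not reproduce.

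**Step 1: share of the window after the infraction.** Let L be the days from infraction to baseline visit (not stated; range assumed). Share = min(L,14)/14. Follow-ups scheduled from baseline fall L+45 and L+90 days after the infraction.

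| L (days) | Post-infraction share | Follow-ups, days from infraction |
|---|---|---|
| 0 | 0% | 45, 90 |
| 3 | 3/14 = 21% | 48, 93 |
| 7 | 7/14 = 50% | 52, 97 |
| 14 | 14/14 = 100% | 59, 104 |
| 30 | 100% | 75, 120 |

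**Step 2: what cancels.** Take the power section's ratios (2.10.12) of follow-up to baseline use: 0.8 exposed and 1 unexposed. If a common lag and fall lower both baselines by 15%, the ratio of ratios is (0.8/0.85)/(1/0.85) = 0.80, unchanged. A common shift in baseline log-odds likewise drops out of the interaction.

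**Step 3: what does not cancel.** Assume true pre-infraction use of 40% of days in both phases, a 30% fall once caught, and mean lags of 3 days in one phase and 5 in the other. None of these values is in the article.

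- Observed baseline at 3 days: 0.40 × (1 − 0.30 × 3/14) = 0.3743; odds 0.3743/0.6257 = 0.598.
- Observed baseline at 5 days: 0.40 × (1 − 0.30 × 5/14) = 0.3571; odds 0.3571/0.6429 = 0.556.
- Spurious odds ratio: 0.598/0.556 = 1.08.

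This is a marginal calculation; the planned model is conditional on student and school effects, so it shows scale only. A longer lag in the exposed phase lowers that baseline and counts against iDECIDE. A longer lag in the unexposed phase gives the reciprocal, 1/1.08 = 0.93, and favours it.

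**Step 4: range.** With use from 0.2 to 0.6 and falls of 20% to 30%, the same 3- versus 5-day difference gives:

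- Low end: baselines 0.2 × (1 − 0.2 × 3/14) = 0.1914 and 0.2 × (1 − 0.2 × 5/14) = 0.1857; odds 0.2367/0.2281 = 1.04.
- High end: baselines 0.6 × (1 − 0.3 × 3/14) = 0.5614 and 0.6 × (1 − 0.3 × 5/14) = 0.5357; odds 1.280/1.154 = 1.11.

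With an equal 7-day lag but a 20% fall in one phase and 30% in the other:

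- Use 0.2: baselines 0.18 and 0.17; odds 0.2195/0.2048 = 1.07.
- Use 0.6: baselines 0.54 and 0.51; odds 1.174/1.041 = 1.13.

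**Step 5: comparison with the threshold.** At 40% use, an odds ratio of 1.045 moves the odds from 0.6667 to 0.6967, which is a probability of 0.4106. That is 0.0106 × 14 = 0.15 days out of 14.

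**Step 6: whether the data allow re-anchoring.** A 14-day window ending the day before the infraction reaches back L + 14 days from the visit. The 90-day recall covers it for L up to 90 − 14 = 76 days.

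**The case against.** The strongest reply is that 2.10.1 uses shorthand for the three visits, not a second schedule. It equates baseline with time-of-infraction, and 2.1 and 2.8 state the aim of holding baseline close to the infraction so that it reflects behaviour at that time. Visit windows and the exact derivation of the 14-day count are commonly left to a full protocol or analysis plan, and the Timeline Followback would support either anchor. This stands in part: the intention limits the lag, and nothing shows that the lag is long. It does not remove the conflict, because the article states two origins and treats a post-consent visit as untreated. An unseen document cannot make both statements true.

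Three stronger inferences are tempting, and the article does not support them.

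- **Baseline understatement as the bias.** One could multiply the shares by an assumed 30% fall, giving about 6%, 15% and 30% at 3, 7 and 14 days, and set that against the planned 20% reduction. That compares a within-phase shift with a between-phase contrast; if the shift is common to both phases, it cancels.
- **Loss of power.** Large losses appear only if the full exposed-phase reduction is assumed to start on the day of the infraction. Nothing in the article says it does.
- **iDECIDE already under way at baseline.** Section 2.7.1 shows that the response may be known by the visit, not that a suspension has been served or a module attended. No start date relative to the visit is given.

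**Conclusion.** The point holds in a limited form. The analysis and design sections anchor the time points on different dates, and a visit-anchored 14-day window puts min(L,14)/14 of the value coded as untreated after the infraction. A lag and fall common to both phases largely cancel in the primary interaction. A difference by phase biases it, in either direction, and could create or hide non-inferiority.

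The size depends on quantities the article does not give. Under the assumed 40% use, 30% fall and lags of 3 versus 5 days, the spurious odds ratio is about 1.08; over the ranges examined it runs from 1.04 to 1.13, about as large as the 1.045 threshold or larger. These figures show sensitivity and are not an estimate of bias. A differential lag or early response is plausible but not documented. The matter should be settled before the analyst is unblinded.

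**What to change.** 1. **Baseline use.** Define it as the 14 days ending the day before the index infraction, derived from the 90-day Timeline Followback already collected at enrolment. Keep the 14 days before the visit as a sensitivity analysis, because that window is the one aligned with the V1 urine sample.
2. **One anchor.** Use the same anchor date for V2 and V3 in 2.1, 2.8 and 2.10.1.
3. **Lag.** Report the infraction-to-V1 interval by study phase.
4. **Knowledge.** This score has no recall window and cannot be re-anchored. Record and report by phase whether V1 preceded the first iDECIDE session. Do not exclude students on that basis: essentially only exposed-phase students could be removed, which would break the intent-to-treat comparison in 2.10.4.

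The cost is a derived variable, two descriptive summaries and consistent wording, all of which can be settled in the analyst-blind period described in 2.6. There are two downsides. Recall is slightly longer when the visit is late, and baseline self-report in the primary analysis no longer matches the period that the V1 urine sample verifies.

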#### 2.10.2. Model specifics—knowledge of drug effects

The average log-odds for probability of obtaining an item correct at each time point will be further decomposed by including, at a minimum: (1) a student-varying intercept to control for individual differences in substance use, (2) an item-varying intercept controlling for differences in difficulty between questions, (3) a school-varying intercept controlling for differences in policy in disciplinary actions and substance use culture across schools, and (4) fixed effects implementing a quadratic time trend over the number of months since the start of the study. If necessary, additional terms (i.e., an interaction between time point and intervention or covariates) can be incorporated.

#### 2.10.3. Model specifics—frequency of substance use

The average log-odds for probability of use at each time point will be further decomposed by including, at a minimum: (1) a student-varying intercept to control for individual differences in substance use, (2) a school-varying intercept controlling for differences in policy in disciplinary actions and substance use culture across schools, (3) fixed effects implementing a quadratic time trend over the number of months since the start of the study, and (4) fixed effects describing differences in days spent using over the three types of substances (alcohol, cannabis, and nicotine). Additional terms (i.e., an interaction between time point or substance type and intervention or covariates) can be incorporated as necessary.

#### 2.10.4. Effect of iDECIDE

The primary effects of interest are whether, for students assigned to the iDECIDE program after their first substance use infraction vs. students who receive standard disciplinary actions, there is (a) an increase in knowledge about substances and their impact and (b) a reduction in days spent using. Effects will be examined using a fixed effect coded as 0 at the *time-of-infraction* and for follow-up time points pre-intervention and coded as 1 at the *45-day-follow-up* and *90-day-follow-up* time points post-intervention. The primary analysis will be the interaction of this variable with a variable indicating whether the school district is in the exposed phase of the study.

We will use an intent-to-treat design. We will examine any student with a substance use infraction in the exposed phase irrespective of actual attendance in the program. Data for primary analyses will only be considered from the first infraction on record.

The study will be conducted as (a) a superiority study on the knowledge endpoint, and (b) a non-inferiority trial on the substance use endpoint. Statistical significance will be defined as a two-sided posterior *p* < 0.025. The non-inferiority margin for substance usage was determined via the fixed margin method (43). Evan-Whipp et al. (44) report results from the International Youth Development Study on what school discipline policies predict reductions in cannabis use. Two discipline approaches significantly predicted a reduction in cannabis use: lecture from teacher (OR = 0.61, 95% CI = 0.45 to 0.83) and police involvement (OR = 0.74, 95% CI = 0.55 to 1.00). The pooled results (OR = 0.68, 95% CI = 0.50 to 0.92) suggest a lower margin of 1.09. Corresponding analyses for alcohol (45) and cigarette use (46) found no significant discipline approaches that predicted reduced use after adjusting for confounders. Using a preserved effect of 50% per FDA guidelines, the minimum non-inferiority threshold based on previous literature is an odds ratio of 1.045.

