#### 2.10.8. Inverse probability weights

The longitudinal aspect of the study design, combined with an inherent possibility of treatment contamination, results in a risk that sample characteristics may differ between the start of the study and the end of the study. For example, in the initial months of the program, the sample will consist of a mix of students more and less responsive to the intervention. However, in later months, students who would be more responsive to the intervention but have not yet committed an infraction could be influenced by students who already received the intervention, and thereby become less likely to commit infractions in the first place. In this scenario, sample characteristics will thereby shift in later months to consist more of less responsive students, resulting in biased estimates that do not properly reflect the efficacy of the study.

We can correct for potential bias due to differing sample characteristics via inverse probability weights (48). Note, however, that standard methods for inverse probability weights (IPW) do not translate easily to Bayesian settings. Therefore, we will either fully implement the two-step method proposed by Liao and Zigler (49), or if computational challenges make this infeasible, implement a pseudo-Bayesian approach. The first step will be to compute the IPW by re-administering a custom school-wide survey (used as part of screening) to students who are enrolled in the study. We will fit a logistic regression predicting referral status (pre- vs. post-intervention) for each student using the following predictors from the survey: (1) whether a student is an athlete (yes or no), (2) a student's grade-point average, (3) a student's post-graduation plans (four-year college, two-year college, trade school, military, getting a job, unknown, and an “other” category), (4) prior suspensions (none, drug-related, and other), (5) race, and (6) ethnicity.

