#### 2.10.10. Sensitivity analyses

For all outcomes, we will conduct at least five sensitivity analyses. We will examine how robust our conclusions are to implementation of the intent-to-treat approach and also conduct an as-treated analysis, restricting comparisons for the key effect to students confirmed to have received standard disciplinary action pre-intervention vs. students confirmed to have attended iDECIDE sessions post-intervention. We will examine how robust our conclusions are to the assumption of additivity with the quadratic time trend and will fit an interaction model to examine (a) the statistical significance of the interaction terms between the key comparison and the quadratic time trend, and (b) the difference in performance on the leave-one-out cross-validation (LOO-CV) approximation between the additive and interaction models. We will examine how robust our conclusions are to the assumption of additivity with the three types of substances (alcohol, nicotine, and cannabis) and will again fit an interaction model and examine (a) the statistical significance of the interaction terms between the key comparison and the categorical predictors for substance type, and (b) the difference in performance on the LOO-CV approximation between the additive and interaction models. We will examine how robust our conclusions are to our missing data approach, rerunning the primary analysis using only observed data. Finally, we will examine how robust our conclusions are to implementation of the IPW approach, rerunning the primary analysis without inclusion of the stabilized weights.

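### The stated primary term duplicates itself: the effect variable in 2.10.4 is already follow-up × exposed phase, so its interaction with exposed phase is the same column

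*Protocol article*

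**What the plan says.** Section 2.10.4 of the protocol article builds the primary test in two sentences. The first begins "Effects will be examined using a fixed effect coded as 0 at the" time of infraction, goes on "and for follow-up time points pre-intervention and coded as 1 at the" 45- and 90-day follow-ups, and limits that value of 1 to follow-ups after the intervention. The second names the tested term: "The primary analysis will be the interaction of this variable with a variable indicating whether the school district is in the exposed phase". The same section sets the intent-to-treat rule: "We will examine any student with a substance use infraction in the exposed phase irrespective of actual attendance in the program".

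Two other sections show what pre- and post-intervention mean in this article. The as-treated analysis in 2.10.10 compares "students confirmed to have received standard disciplinary action pre-intervention vs. students confirmed to have attended iDECIDE sessions post-intervention". The weighting model in 2.10.8 is a regression "predicting referral status (pre- vs. post-intervention) for each student". Both use the terms for study phase.

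Sections 2.10.2 and 2.10.3 list minimum model terms: varying intercepts, a quadratic calendar trend and, for use, substance type. A product of time point and intervention appears only as an optional addition. Section 2.10.1 places a trivariate normal on the log-odds at the three visits and gives, as an example of its priors, "standard deviations for log-odds will be set to 2.5, estimates for fixed effects will be centered at 0".

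**The concern.** The effect sought is a difference in differences: the change from infraction to follow-up in the exposed phase, minus the same change in the unexposed phase. That needs a follow-up indicator that is on in both phases, so that unexposed students supply the comparison change. The variable in 2.10.4 is off at every unexposed follow-up, so it already contains the phase contrast, and a second multiplication by phase adds nothing.

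These two sentences define the test for both primary outcomes, superiority on knowledge and non-inferiority on use, and so feed every row of Table 3. Two analysts could fit different models from them. Some change is expected without iDECIDE: scores can rise when a knowledge survey is repeated, and use measured close to being caught can regress towards the mean.

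**Working it through.** **Inputs.** The coding, the tested term, the 0.025 two-sided level and the 1.045 threshold are from 2.10.4. The prior is from 2.10.1 and the ratio 0.8 from 2.10.12. The article gives no figure for this coefficient, so there is none to reproduce.

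**Step 1: the coding.** Let F = 1 at the 45- and 90-day visits, E = 1 in the exposed phase, and V be the variable as coded.

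| Observation | F | E | V | V × E |
|---|---|---|---|---|
| Infraction, unexposed | 0 | 0 | 0 | 0 |
| Follow-up, unexposed | 1 | 0 | 0 | 0 |
| Infraction, exposed | 0 | 1 | 0 | 0 |
| Follow-up, exposed | 1 | 1 | 1 | 1 |

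V = F × E, so V × E = F × E × E = V in every row.

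**Step 2: rank.** An illustrative stepped wedge was built with seven clusters crossing every three months, infractions spread over 27 months, visits at 0, 1.5 and 3 months, a quadratic trend and cluster effects.
- V, E and V × E: rank 11 of 12 columns. Adding F: 12 of 13.
- F, E and F × E: rank 12 of 12.

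**Step 3: both terms fitted.** Assume the example prior means N(0, 2.5²) on each fixed effect. Let s be the sum of the two coefficients and d their difference. Each has prior variance 2 × 2.5² = 12.5, and the data update s only. The tested coefficient is half of s minus d, so its posterior variance is (Var(s | data) + 12.5)/4.
- Assume s is estimated with SE between 0.05 and 0.20. Then Var(s | data) = 1/(1/12.5 + 1/SE²), which is 0.0025 to 0.0399.
- Posterior SD: √(12.5025/4) = 1.768 to √(12.5399/4) = 1.771.
- Take a total effect of log(0.8) = −0.223 for illustration (the 0.8 in 2.10.12 is a ratio of proportions of days, not an odds ratio). The posterior mean is about −0.223/2 = −0.11.
- The 97.5% interval is −0.11 ± 2.2414 × 1.768, about −4.07 to +3.85. The probability of an odds ratio below 1.045 is about 0.535 at every SE in the range.
- For this coefficient to reach the 0.025 level, the total effect would have to be about 2 × 2.2414 × 1.768 = 7.9 log-odds.

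The posterior is proper, so the program would run and return these numbers.

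**Step 4: product entered once.** With E and F × E but no F, the matrix is full rank (11 of 11). With a common follow-up change of −0.30 log-odds and no treatment effect, the product's coefficient is −0.30. With F added it is 0 and F takes the −0.30.

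**Step 5: V by phase at the visit, E by phase at the infraction.** The matrix is full rank (12 of 12). V and V × E then differ only for students whose follow-up falls after a switch that came after their infraction, 189 of 3,402 rows in the illustration. With a true effect of log(0.8) at every post-switch follow-up, the product's coefficient is 0: it contrasts exposed students with those who straddle the switch.

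**The case against.** The strongest reply is that intervention in 2.10.4 means the school's response of either kind. Section 2.7 lists discipline as usual under interventions, and 2.10.7 speaks of time points after discipline. V would then be a before/after-response indicator in both phases and V × E the usual difference in differences. This is probably what was intended. It does not fit the text, though. Section 2.1 places the follow-ups after the school response, so the group of follow-ups before the intervention, which 2.10.4 expressly codes 0, would be essentially empty. Sections 2.10.8 and 2.10.10 also use the terms for phase. Reading intervention as a student's own receipt of iDECIDE does not help either: V = 1 would still imply an exposed district, and the coding would conflict with the intent-to-treat sentence.

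Three parts of the reply stand:
- Non-identification needs both identical columns in the model. The article gives no formula, and an analyst working on shuffled data (2.6) might notice the duplication.
- The SD of 2.5 is given only as an example, so 1.77 illustrates the problem and does not predict a result.
- The models in 2.10.2 and 2.10.3 are minimum lists, and a trivariate normal may carry visit-specific means. The absence of visit and phase main effects from those lists is therefore not a fault in itself.

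**Conclusion.** The primary term as worded is wrong and needs correcting before the analyst is unblinded. On the meaning of pre- and post-intervention used elsewhere in the article, the variable and its interaction are one column. What follows depends on how the text is implemented:
- With both terms fitted, the tested coefficient carries about half the effect, with an SD of about 1.77 log-odds that more data would not reduce materially (given a normal prior with SD 2.5).
- With the product entered once, the effect is identified, but it absorbs any baseline-to-follow-up change shared by the two phases unless the model has visit means common to both.

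A reader might infer that neither primary hypothesis can be declared. The documents do not support that: it would require both duplicate columns to be fitted, the prior-driven coefficient to be reported and the example prior to be kept. Nor do they show that natural change will be credited to iDECIDE, since visit-specific means may be planned. No share of unexposed students crossing over before their last visit is claimed, because step lengths are given only as approximate school months and the length of the transition periods is not stated.

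**What to change.** Reword the coding in 2.10.4, and make the model statements in 2.10.2 and 2.10.3 agree with it:
- F = 1 at the 45- and 90-day visits in both phases, and 0 at the time of infraction.
- E = 1 if the district was in the exposed phase on the date of the student's first infraction, held fixed for all of that student's visits. This matches the intent-to-treat sentence.
- Include the visit (F) and phase (E) main effects, and name F × E as the primary effect for both outcomes.

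The cost is wording and model code. Design, data collection and sample size do not change. It should be done during the analyst-blind period described in 2.6, because choosing between the readings after unblinding would be a data-dependent choice of the primary effect.
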